# Treatment with PBI-4050 in patients with Alström syndrome: study protocol for a phase 2, single-Centre, single-arm, open-label trial

**DOI:** 10.1186/s12902-018-0315-6

**Published:** 2018-11-26

**Keywords:** Alström syndrome, Fibrosis, Insulin resistance, Metabolic syndrome, Diabetes mellitus, Obesity, Cardiovascular, Liver, Magnetic resonance imaging, PBI4050

## Abstract

**Background:**

Alström syndrome (ALMS) is a very rare autosomal recessive monogenic disorder caused by a mutation in the *ALMS1* gene and characterised by childhood onset obesity, dyslipidaemia, advanced non-alcoholic fatty liver disease, diabetes and extreme insulin resistance. There is evidence of multi-organ fibrosis in ALMS and severity of the disease often leads to organ failure with associated morbidities, resulting in reduced life expectancy. There are no specific treatments for this disease, and current management consists of only symptomatic therapies. PBI-4050 is a new molecular entity with demonstrated anti-inflammatory and anti-fibrotic activities in preclinical models, including animal models of human diseases characterized by progressive fibrosis in the kidney, heart, liver and lungs. Moreover, completed Phase 2 studies in type 2 diabetes mellitus with metabolic syndrome and idiopathic pulmonary fibrosis further support the anti-inflammatory and anti-fibrotic activity of PBI-4050. Together, these data suggest that PBI-4050 has the potential to treat the pathological inflammatory and fibrotic features of ALMS. The aim of this study is to evaluate the safety and anti-inflammatory & anti-fibrotic activities of PBI-4050 in subjects with ALMS.

**Methods:**

This is a Phase 2, single-centre, single-arm, open-label trial. A total of 18 patients with ALMS will be enrolled to receive PBI-4050 at a total daily oral dose of 800 mg for an initial 24 weeks with continuation for an additional 36 or 48 weeks. Standard assessments of safety include adverse events, clinical laboratory tests, vital signs, physical examination and electrocardiograms. Efficacy assessments include adipose tissue biopsy, hyperinsulinaemic-euglycaemic glucose clamp, adipose tissue microdialysis, liver transient elastography, liver and cardiac magnetic resonance imaging, and laboratory blood tests.

**Discussion:**

This is the first clinical study of PBI-4050 in subjects with ALMS. Given the rarity and complexity of the disease, a single-centre, single-arm, open-label design has been chosen to maximise subject exposure and increase the likelihood of achieving our study endpoints. The results will provide valuable safety and preliminary evidence of the effects of PBI-4050 in ALMS, a rare heterogeneous disease associated with progressive fibrosis and premature mortality.

**Trial registration:**

The trial is registered on ClinicalTrials.gov (Identifier; NCT02739217, February 2016) and European Union Drug Regulating Authorities Clinical Trials (EudraCT Number 2015–001625-16, Sept 2015).

**Electronic supplementary material:**

The online version of this article (10.1186/s12902-018-0315-6) contains supplementary material, which is available to authorized users.

## Background

Alström syndrome (ALMS) is a rare autosomal recessive genetic disorder with an estimated prevalence of less than one per million [1]. It is characterized by retinal cone-rod dystrophy, hearing loss, childhood obesity, hyperinsulinemia, severe insulin resistance, as well as type 2 diabetes mellitus (T2DM), hypertriglyceridemia and multiple organ dysfunctions due to progressive fibrosis. Increasing systemic fibrosis develops as patients age, with clinical manifestations in multiple organs. The severity of the disease, often leading to organ failure with associated morbidities, results in a reduced life expectancy, rarely exceeding 50 years [1]. There is no specific treatment for this genetic disease and current management consists of symptomatic therapies.

ALMS is caused by mutations in ALMS1, a large gene located on chromosome 2p13 with ubiquitous expression [2, 3]. The ALMS1 protein localizes to the centrosomes and basal bodies of ciliated cells and may play a role in microtubular organization and cilia assembly or function [3, 4]. In addition, this protein has been implicated in intracellular trafficking, regulation of cilia signalling pathways, and cellular differentiation among others [5]. Pathological observations from post-mortem specimens reveal extensive fibrosis in many organs including the kidney, heart, liver, and lung [6]. Furthermore in vitro dermal fibroblast cultures from ALMS patients display cytoskeleton abnormalities, impaired migration, increased production of collagens, have augmented cell cycle length, and show enhanced resistance to apoptosis [7].

PBI-4050 is a potential drug candidate for the treatment of inflammatory and fibrosis-related diseases, including idiopathic pulmonary fibrosis, chronic kidney disease and T2DM with metabolic syndrome. PBI-4050 is a 3-pentylbenzeneacetic acid sodium salt with a molecular weight of 228.3. It is a new molecular entity with demonstrated anti-inflammatory and anti-fibrotic activities in both in vitro and in vivo models. In vitro models have shown that PBI-4050 regulates macrophages, T cells, fibrocytes, fibroblasts, myofibroblasts, and epithelial cells and modulates the over-expression of many pro-inflammatory and pro-fibrotic cytokines and growth factors in different cell types [8–10]. Moreover, when tested against normal human dermal fibroblasts stimulated with transforming growth factor- β, PBI-4050 markedly reduced the production of pro-fibrotic cytokines, including connective tissue growth factor (CTGF) and epidermal growth factor, while restoring the production of anti-fibrotic cytokines such as hepatocyte growth factor [11–14]. PBI-4050 also reduced the production of α-smooth muscle actin, a marker of myofibroblast activity [15]. Pre-clinical testing has shown PBI-4050 to be effective in preventing or reversing fibrosis in all animal models studied, including models of fibrosis in the heart, kidney, lung and liver [12, 13, 16–21]. Furthermore, PBI-4050 has been shown in a spontaneous model of T2DM (the *db*/*db* mouse) to be effective in preventing the loss of insulin production that characterizes the natural history in these animals and leads to death from hyperglycaemia at 24 to 26 weeks of age [22, 23]. Late treatment (from 16 weeks of age) with PBI-4050 restores insulin production and preserves the islet architecture by reducing macrophage and T-cell infiltration [9, 16].

Thus, the available pre-clinical data suggest that PBI-4050 has the potential to treat the pathological inflammatory and fibrotic features of ALMS as outlined in Table 1. Many of these features will be explored in this study as well. The anti-fibrotic effects of PBI-4050 will be assessed by measuring blood and urine biomarkers of fibrosis and inflammation and by performing imaging studies such as transient elastography (TE) or fibroscan of the liver and magnetic resonance imaging (MRI) of the heart and liver. The potential effects on insulin sensitivity will be assessed by standard clinical and research methods, including fasting blood glucose, 4-point glucose profile, hyperinsulinaemic-euglycaemic clamp and adipose tissue microdialysis. The data generated will provide valuable evidence to support further development of PBI-4050 for the treatment of ALMS.

**Table 1 Tab1:** Major clinical manifestations of Alström syndrome and corresponding pre-clinical effects of PBI-4050

Clinical features of ALMS	Corresponding pre-clinical effects of PBI-4050
Loss of organ function due to fibrosis involving	
Heart	↓ heart fibrosis in suprarenal aortic banding in rats
Lung	↓ lung fibrosis in bleomycin-induced lung fibrosis in mice
Liver	↓ liver fibrosis in CCl4-induced liver fibrosis in rats
Kidneys (renal failure)	↓ kidney fibrosis in various animal models of kidney fibrosis
Type 2 diabetes mellitus	
Early hyperinsulinemia	Reduces insulin resistance in db/db diabetic mice and db/db eNOS−/− diabetic mice
Severe insulin resistance	Normalizes glycaemia in diabetic mice
Late pancreatic failure	Maintains (early treatment) or restores (late treatment) insulin content in pancreatic islets

*eNOS*^*−/−*^ endothelial nitric oxide synthase knockout (mice)

The actual clinical benefits and risks of PBI-4050 are currently unknown in subjects with ALMS, as this is the first study in this subject population. Given the lack of effective treatment for multi-organ fibrosis, a characteristic of ALMS, the proposed study of PBI-4050 is justified based on pre-clinical efficacy data in animal models of fibrosis. Early clinical studies suggest that PBI-4050 is safe and well tolerated after single-dose oral administration at doses ranging from 400 to 2400 mg in healthy volunteers (*n* = 30) and after repeat daily oral doses of 800 mg in subjects with stable renal impairment (*n* = 6), T2DM with metabolic syndrome (*n* = 41), and idiopathic pulmonary fibrosis (*n* = 26), with preliminary evidence of clinical activity in the latter two studies [24, 25]. Across these studies, there have been no deaths but one subject had a study drug-related treatment-emergent serious adverse event (SAE) of pneumonia. Most adverse events (AEs) were mild or moderate in severity, with headache, insomnia, diarrhoea, somnolence, fatigue, and dizziness being the most frequent study drug-related AEs. In addition, there were no clinically significant changes in clinical laboratory, vital signs, or ECG parameters.

### Study objectives

The primary objective is to evaluate the safety and tolerability of 800 mg PBI-4050 (Investigational Medicinal Product [IMP]), administered orally once daily.

The secondary objectives are:To evaluate the effect of the IMP on metabolic syndrome parametersTo evaluate the effect of the IMP on pro-inflammatory/inflammatory, fibrotic, diabetic, and obesity biomarkers in blood and urineTo evaluate the effect of the IMP on antidiabetic treatment, including oral therapy and insulin requirements

The exploratory objectives are:To examine the effect of the IMP on the histological appearances of fat biopsies, in particular the degree of fibrosis and macrophage infiltration;To analyse the effect of the IMP on the global metabolome using systemic blood and adipose tissue-specific microdialysis samples;To analyse the effect of the IMP on the microdialysate fractions using adipose tissue microdialysis samples;To assess the effect of the IMP on liver stiffness using transient elastography;To measure the effect of the IMP on the fat content and fibrosis burden in the liver using MRI;To measure the effect of the IMP on cardiac fibrosis and function using MRI and on biomarkers, including N-terminal pro-brain natriuretic peptide (NT-pro-BNP);To evaluate the effect of the IMP on additional pro-inflammatory/inflammatory, fibrotic, diabetic, and obesity biomarkers in blood and urine;To evaluate the effect of the IMP on glucose, insulin, and lipid dynamics using the hyperinsulinaemic-euglycaemic clamp test.

## Methods

Study PBI-4050-ATX-9-05 is a Phase 2, single-centre, single-arm, open-label study of PBI-4050 in subjects with ALMS. The initial duration of the study is 24 weeks and subjects can elect to enrol into an extension phase of 36 or 48 weeks and subsequently into the ALMS rollover study PBI-4050-CT-9-10. The schedule of study procedures for the enrolment, intervention, and assessments for participants is outlined in Fig. 1 and Table 2 and presented in detail in Additional file 1 (main study) and Additional file 2 (extension period). Subjects will be considered enrolled in the main study at the point when they give written informed consent and treatment with study drug has commenced. Each subject will then be assigned a unique identification number with a country code, site number, and subject number. Subjects may only be included in the 36- or 48-week extension period if informed consent is obtained in advance of any additional study-specific procedures.

**Fig. 1 Fig1:**
[figure not shown]
Flowchart of study design

**Table 2 Tab2:** Study visits

Visit	Screen	Wk 1	Wk 4	Wk 8	Wk 12	Wk 16	Wk 20	Wk 24	EP 12	EP 24	EP 36	EP 48	EoS
Informed consent	X							X					
Demography and History	X												
Physical examination	X	X			X			X	X	X	X	X	X
Vital signs	X	X	X	X	X	X	X	X	X	X	X	X	X
Weight & waist	X	X	X	X	X	X	X	X	X	X	X	X	X
Haematology/Biochemistry	X	X	X	X	X	X	X	X	X	X	X	X	X
Urinalysis	X	X	X	X	X	X	X	X	X	X	X	X	X
12-lead ECG	X	X			X			X	X	X	X	X	X
IMP accountability		X	X	X	X	X	X	X	X	X	X	X	
Fasting glucose profile		X	X	X	X	X	X	X	X	X	X	X	X
Adverse events		X	X	X	X	X	X	X	X	X	X	X	X
Concomitant medications		X	X	X	X	X	X	X	X	X	X	X	X
FibroScan		X			X			X	X	X	X	X	
Liver/Cardiac MRI		X						X			X		
Insulin clamp/Microdialysis		X						X					
Adipose tissue biopsy		X						X					
Metabolic syndrome parameter		X			X			X	X	X	X	X	
Biomarkers		X	X	X	X	X	X	X	X	X	X	X	

*Screen* Screening visit, *Wk* weeks, *EP* Extension phase visits

### Location and setting

Study PBI-4050-ATX-9-05 is sponsored by Prometic Biosciences and subjects are recruited from the clinical service at University Hospitals Birmingham NHS Foundation Trust, United Kingdom (UK), which is a nationally commissioned specialist service for ALMS.

### Study population and eligibility criteria

A total of 18 subjects will be enrolled. Subjects should fulfil the following criteria:16 years of age or older at screening;A diagnosis of ALMS, confirmed by genetic testing before screening;Subjects on diabetes treatment are receiving the same antidiabetic agent for a minimum of 1 month before screening;Able and willing to self-monitor blood glucose level with or without assistance;Female subjects of childbearing potential must have a negative pregnancy test and agree to use adequate birth control throughout the study and for 30 days after the last dose of study drug;Male subjects are willing to use an acceptable contraceptive method throughout the study and for 30 days after the last dose of study drug;Able to give written informed consent.

Subjects will not enter the study if any of the exclusion criteria listed in Additional file 3 is fulfilled.

### Intervention

PBI-4050 is administered at a total daily oral dose of 800 mg, 1 h before or 2 h after a meal. Subjects are encouraged to take PBI-4050 consistently at the same time every day. Subjects are prohibited from taking the following concomitant medications:Weight loss medications, including natural products;Moderate/potent cytochrome P450 (CYP) 2C9 inhibitors (e.g., amiodarone, fluconazole, miconazole, and oxandrolone) and moderate/potent CYP2C9 inducers (e.g., carbamazepine and rifampin);Strong CYP3A inhibitors (e.g., ketoconazole, itraconazole, clarithromycin) and strong CYP3A inducers (e.g., rifampin, phenytoin, carbamazepine, and St. John’s wort).

### Study procedure

#### Assessment of safety and tolerability

AEs will be assessed by the investigator starting from screening through 30 days after the last dose of study drug. AEs occurring at the time of the first dose of study drug are referred to as treatment-emergent AEs.

A complete physical examination along with ECGs and vital signs will be performed at each visit. Fasting blood and urine samples will also be collected at each visit for monitoring safety, including haematology, biochemistry, and urinalysis. Clinically significant changes in any of these parameters will be recorded as AEs.

Haematology includes complete blood cell count (CBC), which includes red blood cell count (RBC), haematocrit, and haemoglobin; white blood cell (WBC) count with 5-part differentials (absolute values); and platelet count. Biochemistry includes electrolytes (calcium, sodium, potassium, phosphate, and magnesium), liver function (aspartate aminotransferase [AST], alanine aminotransferase [ALT], gamma-glutamyl transferase [GGT], and total bilirubin), other enzymes and substrates (alkaline phosphatase [ALP]), urea, uric acid, creatinine, albumin, and lactate dehydrogenase, and lipid profile (total cholesterol, HDL-C, low-density lipoprotein cholesterol [LDL-C], triglycerides, total plasma protein).

Urinalysis will include the following macroscopic examinations: pH, specific gravity, protein, glucose, ketones, blood, nitrite, and leukocytes. If the macroscopic shows any abnormal findings, microscopic examination will be performed. Urine pregnancy test will be performed for women with childbearing potential.

Study subjects will be instructed to measure fasting blood glucose each morning and 4-point blood glucose profiles weekly, with the results recorded in a diary. Study personnel will contact the subjects by phone weekly to review the blood glucose results. Subject diaries will be reviewed at each study visit. Hypoglycaemic episodes will be classified as AEs of special interest and defined as follows:Suspected symptomatic hypoglycaemia: Symptoms of hypoglycaemia (shaking, dizziness, blurred vision, palpitations, sweating, etc.) with no confirmatory blood glucose level, or blood glucose 3.5–3.9 mmol/L with or without symptoms.Confirmed hypoglycaemia: Blood glucose < 3.5 mmol/L with or without symptoms (shaking, dizziness, blurred vision, palpitations, sweating, etc.).Severe hypoglycaemia events: Blood glucose < 3.0 mmol/L and/or loss of consciousness.

Details of safety endpoints will be captured on the study electronic case report form.

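### The category named suspected symptomatic hypoglycaemia admits asymptomatic readings, and the loss-of-consciousness limb of the severe category has no glucose or causality condition

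*Protocol article*

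**What the plan says.** The primary objective concerns safety (Study objectives): "The primary objective is to evaluate the safety and tolerability of 800 mg PBI-4050". Within the safety assessments, hypoglycaemia is the one event type that the article singles out: "Hypoglycaemic episodes will be classified as AEs of special interest and defined as follows". Three definitions follow in Assessment of safety and tolerability:

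- **Suspected symptomatic.** This opens with "Suspected symptomatic hypoglycaemia: Symptoms of hypoglycaemia" in the absence of a confirmatory glucose value, and then adds a second limb: "or blood glucose 3.5–3.9 mmol/L with or without symptoms".
- **Confirmed.** "Confirmed hypoglycaemia: Blood glucose < 3.5 mmol/L with or without symptoms". There is no lower bound.
- **Severe.** "Severe hypoglycaemia events: Blood glucose < 3.0 mmol/L and/or loss of consciousness". The second limb carries no further condition.

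The same section has subjects measure fasting glucose each morning and a 4-point profile each week, recorded in a diary. These measurements are scheduled and do not depend on symptoms. Sample size and statistical analysis reports categorical variables as numbers and percentages.

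**The concern.** The label of the first category and its second limb contradict each other: a category called symptomatic accepts readings without symptoms. Because most self-monitoring is routine, such readings can be expected to arise from the schedule itself. A reader of the safety table would take the suspected symptomatic row as a count of subjects who felt unwell, when some or most of its entries could be diary values that nobody noticed.

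The severe category raises a second problem. Loss of consciousness alone satisfies it, with no glucose value and no judgement of cause required. Alström syndrome involves cardiac fibrosis (Background), and the withdrawal criteria anticipate falls in heart rate or blood pressure with cardiovascular symptoms. A non-glycaemic loss of consciousness is therefore a realistic possibility in this population.

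With no control arm, these counts have to be read on their own, so their labels must mean what they say.

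**Working it through.** There is no planned figure to reproduce, so the check is logical. Write g for glucose in mmol/L and LOC for loss of consciousness. Taken literally, the definitions are:

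- Suspected symptomatic: (symptoms and no g) or 3.5 ≤ g ≤ 3.9
- Confirmed: g < 3.5
- Severe: g < 3.0 or LOC

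Applied to a grid of values (none, 2.9, 3.0, 3.4, 3.5, 3.9, 4.0, 6.0), each with and without symptoms and LOC:

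| Glucose | Symptoms | LOC | Categories met |
|---|---|---|---|
| none | yes | no | Suspected symptomatic |
| none | no | yes | Severe |
| none | yes | yes | Suspected symptomatic and Severe |
| 2.9 | either | either | Confirmed and Severe |
| 3.0 or 3.4 | either | no | Confirmed |
| 3.0 or 3.4 | either | yes | Confirmed and Severe |
| 3.5 or 3.9 | **no** | no | **Suspected symptomatic** |
| 3.5 or 3.9 | yes | no | Suspected symptomatic |
| 3.5 or 3.9 | either | yes | Suspected symptomatic and Severe |
| 4.0 or 6.0 | either | no | none |
| 4.0 or 6.0 | either | **yes** | **Severe** |

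Four results follow.

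1. A reading of 3.5 or 3.9 with no symptoms is classed as suspected symptomatic. No reading of the sentence avoids this.
2. LOC at 4.0 or 6.0, or with no glucose value, is classed as severe hypoglycaemia.
3. The categories are not exclusive: 2.9 meets two of them. They are not cleanly nested either: LOC at 3.5–3.9 is suspected symptomatic and severe but not confirmed, and LOC at 6.0 is severe only.
4. The cut-offs themselves leave no gap between the confirmed range and the 3.5–3.9 band.

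The monitoring schedule shows how many readings are exposed to result 1. Seven fasting readings plus four profile points give 11 a week, or 10 if the fasting value serves as one of the four. Over 24 weeks that is 10 × 24 = 240 to 11 × 24 = 264 readings per subject, and for 18 subjects 240 × 18 = 4,320 to 264 × 18 = 4,752, with full adherence. The article gives no rate of asymptomatic 3.5–3.9 values, so the number mislabelled cannot be derived.

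**The case against.** The strongest reply is that these are wording points in an exploratory study. The study says it tests no hypothesis, the investigator assesses AEs, diaries are reviewed by weekly phone call and at visits, and tabulation rules normally sit in an analysis plan that is not shown. Much of this stands, and it rules out several stronger readings.

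- **That severe events are counted twice.** A reader might infer this because every value below 3.0 meets two definitions. The article does not say that the categories are exclusive or will be summed. For glucose values, severe may be meant as a subset of confirmed. The absence of a counting rule is not in itself a fault in an article.
- **That non-glycaemic syncope will be attributed to hypoglycaemia.** The lead-in speaks of hypoglycaemic episodes and the entry is headed as hypoglycaemia, which suggests a narrower intent. But these sentences are what define such an episode, and none supplies the condition. The claim therefore holds for the literal text, not as a forecast of what investigators will do.
- **That there is no pre-dose hypoglycaemia record.** In Table 2 the row "Fasting glucose profile" starts at Wk 1, which invites this inference. The baseline MRI, clamp and biopsy also first appear at Wk 1. The AE row starts there too, although the text has AEs assessed from screening. The detailed schedule is in an additional file not shown, so the row does not settle the matter.
- **That a particular number of readings will be mislabelled.** Any such figure needs an event rate that the documents do not give.

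What the reply does not remove is the contradiction between label and definition. The definition is printed in full, so condensation does not explain it, and a later tabulation rule would inherit the wrong label.

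**Conclusion.** The point holds on the article's own wording. Asymptomatic readings of 3.5–3.9 mmol/L would be reported as suspected symptomatic events; this is certain from the text. The loss-of-consciousness limb is unconditioned as written, and it is also what prevents a clean nesting of the three categories; here the intent was probably narrower, but it is not stated.

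The consequence is misclassification in descriptive counts of an AE of special interest under the primary objective. No sample size, power or significance level is affected. The size in events is unknown. It depends on how often scheduled readings fall in the 3.5–3.9 band without symptoms, and on whether any non-glycaemic loss of consciousness occurs. The correction is worth making because it is cheap and because symptom status and cause are best recorded when the event is entered.

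**What to change.** Keep the plan's own cut-offs and make three changes.

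1. Reconcile the first label with its content. Keep symptoms without a reading, and symptoms with a 3.5–3.9 reading, under suspected symptomatic. Report asymptomatic 3.5–3.9 readings on a separate line as low readings.
2. Count loss of consciousness as severe hypoglycaemia only when it accompanies a low glucose value, with the sponsor stating which of its existing cut-offs defines low, or when the investigator judges the event hypoglycaemic. Otherwise report it as its own AE.
3. Tabulate each episode once, at the highest category that it meets. This also settles overlaps that remain after change 2, such as a hypoglycaemic loss of consciousness at 3.5–3.9.

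The cost is a small change to the definition wording, the electronic case report form and the programming, plus reclassification of events already recorded. Trial status reports 12 subjects recruited to the main study, so some events may need review. How easily that can be done depends on whether symptoms were recorded beside each reading, which the article does not show.
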